### Intervention group

The participants in the intervention group will enter ePain after completing the baseline assessment and randomization at week 1. They will be able to access all of the contents of ePain throughout the study period. They will complete the process evaluation at week 3, the post assessment at week 6, and the follow-up assessment at week 12.

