### Sample size

The sample size was estimated based on Ruehlman et al. [30], who aimed to examine an Internet-based programme for the self-management of chronic pain in the United States. Their measure of pain intensity was used to calculate the effect size, as their study did not examine self-efficacy. The effect size was calculated to be 0.47. To achieve an effect size of 0.47, a power value of 0.8, and an α value of 5%, 114 participants will be recruited. The drop-out rate has been calculated with reference to Ruehlman et al.’s study examining the efficacy of an online Chronic Pain Management Programme and William et al.’s study evaluating the effects of an Internet-based behavioural self-management programme on fibromyalgia patients [30, 31]. The drop-out rate was 7.5% in Ruehlman et al.’s study and 10% in William et al.’s study [30, 31]. A 30% drop-out rate needs to be considered to obtain an adequate number of participants. Therefore, 148 participants will be recruited, with 74 participants in each group.

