### Statistical methods

The IBM Statistical Package for the Social Sciences (SPSS) for Windows version 25.0 will be used to statistically analyse the quantitative data. Normality checking will be conducted using the Kolmogorov–Smirnov test. For the descriptive data on the demographics and outcome variables, the means, standard deviations, and percentages will be calculated. For continuous variables, the mean and standard deviations will be presented. The median and a centile range will be reported if the continuous variables do not show a symmetrical distribution.

The data will be analysed on an intention-to-treat basis. Generalized estimating equations will be adopted to investigate the time-averaged difference and differences at each follow-up time. An analysis will be conducted of the within-group effect at week 3, week 6, and week 12, and the interaction between the time effect and the group by group effect (group × time) on the outcome variables, including pain self-efficacy, pain situations, negative emotions, and quality of life. An independent-samples *t* test will be conducted for between-group comparisons at week 3, week 6, and week 12. The significance level will be set at 0.05. Missing data will be analysed using Missing Values in SPSS. The last observation carried forward method will be used to replace the missing data [49, 50].

The Consolidated Standards of Reporting Trials (CONSORT) will be adopted to write up the final report.

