## Discussion

Different studies using web-based programmes have demonstrated satisfactory results for their targeted populations [31, 32]. Using web-based programmes to administer health education to the public has become a trend due to the efficiency of this approach in getting in touch with and delivering information to participants [27]. As information technology develops more quickly, both hardware and software will greatly facilitate the spread of information to the public.

This study will adopt the self-efficacy theory of behavioural change to develop an intervention. ePain will provide step-by-step illustrations of pain knowledge and interventions for participants to improve their pain situations. People like to use self-initiated treatments to relieve pain [17]. ePain will provide information about different types of self-initiated treatments, including their correct use. Therefore, this study will use ePain to examine the improvement in the pain self-efficacy of the participants, which previous studies have yet to consider as a primary outcome [30].

The participants in ePain will benefit from improved pain self-efficacy and decreased pain intensity. They will be able to learn and understand pain as they go through the chapters. ePain will introduce various pharmacological and non-pharmacological interventions. The participants will be able to plan and choose their preferred pain relief methods. As psychological distress is associated with pain, the participants will experience lower levels of psychological distress. The anticipated effects of pain management can be sustained; ePain is an electronic pain management programme that will be available on the Internet for the public to access and it will be a cost-effective intervention.

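### Carrying the last score forward partly assumes persistence at week 12, scores early losses on baseline or week 3 values that differ by arm, and treats the copies as observed data

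*Protocol article*

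**What the plan says.** The Statistical methods section fixes the handling of missing outcomes: "Missing data will be analysed using Missing Values in SPSS", and then "The last observation carried forward method will be used to replace the missing data". It limits the rule to no arm, outcome or visit, and states no missingness assumption. The filled data enter every planned analysis. The analysis set is given by the statement "The data will be analysed on an intention-to-treat basis". For the main model the section says "Generalized estimating equations will be adopted to investigate the time-averaged difference and differences at each follow-up time", and for the comparisons by visit it says "An independent-samples *t* test will be conducted for between-group comparisons at week 3, week 6, and week 12".

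The visits decide which score is carried. For the ePain arm: "They will complete the process evaluation at week 3, the post assessment at week 6, and the follow-up assessment at week 12". The Control group section lists only baseline, week 6 and week 12. Data collection methods places the week 3 assessment of self-efficacy and pain in the intervention group and does not list DASS-21 or WHOQOL-BREF there.

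On drop-out, the Sample size section cites 7.5% and 10% from two earlier studies and then says: "A 30% drop-out rate needs to be considered to obtain an adequate number of participants". The Discussion says of the programme: "The anticipated effects of pain management can be sustained".

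**The concern.** Week 12 is the only assessment after the six-week programme ends, so it carries the evidence on persistence. Under this rule, anyone lost after week 6 contributes the week 6 score a second time, and that part of the week 12 result is assumed.

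Earlier losses are scored on stale values that differ by arm. Controls lost before week 6 and ePain participants lost before week 3 are set to no change at weeks 6 and 12. ePain participants lost between weeks 3 and 6 carry week 3 for self-efficacy and pain, but baseline for DASS-21 and WHOQOL-BREF.

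The filled values are then analysed as if 74 per arm had been observed. The result can be a diluted effect, an apparent persistence that is not there, or a difference produced by unequal loss. The primary outcome is affected.

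**Working it through.** **Inputs from the protocol.** Effect 0.47 SD; 74 per arm (114 × 1.3 = 148.2, taken as 148); drop-out 7.5%, 10% and 30%. The protocol gives no figure for the effect of its missing-data rule, so there is none to reproduce. At 74 per arm the copied week 12 values would number 74 × 0.075 ≈ 6, 74 × 0.10 ≈ 7 and 74 × 0.30 ≈ 22 per arm.

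**Assumptions, not in the protocol.** Two-sided 0.05, correlation 0.7 between visits, SD 1 at each visit, loss completely at random within arm, and the timing and shared change stated in each case. Rejection rates in (b) and (c) come from simulation.

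**(a) True effect 0.47 SD, equal loss *d*, no post-baseline score for anyone lost.** Expected estimate = 0.47 × (1 − *d*). Power ≈ Φ(effect × √(n/2) − 1.96), with n = 74 for carried data and 74(1 − *d*) for observed data.

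| Loss | Carried-forward estimate | Power, carried forward | Power, observed scores (effect stays 0.47) |
|---|---|---|---|
| 7.5% | 0.435 | 75% | 79% |
| 10% | 0.423 | 73% | 77% |
| 30% | 0.329 | 52% | 67% |

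For the last row: 0.329 × √37 − 1.96 = 0.04 and Φ(0.04) ≈ 0.52; 0.47 × √25.9 − 1.96 = 0.43 and Φ(0.43) ≈ 0.67. The exact *t* test gives about 51% and 66%; simulation gives 50–51% for the carried data.

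If half of the ePain losses carry a week 3 score that already shows the full effect, the 30% case becomes 0.47 × (0.70 + 0.15) ≈ 0.40 SD, with power about 67%.

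**(b) Effect 0.47 SD at week 6, none at week 12, equal loss after week 6.** Expected week 12 difference = *d* × 0.47. At 10% it is 0.047 SD, significant in about 6% of trials. At 30% it is 0.141 SD, significant in about 13–14%.

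**(c) No treatment effect, shared improvement *s*, unequal loss before any post-baseline score.** Expected difference (ePain − control) = (1 − d_ePain)*s* − (1 − d_control)*s* = (d_control − d_ePain)*s*. With *s* = 0.5 SD:
- losses of 15% v 30%: 0.15 × 0.5 = 0.075 SD, error rate about 7–8%;
- losses of 10% v 40%: 0.30 × 0.5 = 0.15 SD, error rate about 14–15%;
- losses of 7.5% v 10%: 0.025 × 0.5 ≈ 0.01 SD, error rate about 5%.

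The difference runs against the arm with more loss. With *s* = 0.2 and 15% v 30% it is 0.03 SD and the error rate stays close to 5%.

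**(d) Different visits carried.** Suppose ePain produces a passing week 3 gain, there is no week 12 difference, and ePain participants are lost between weeks 3 and 6. The spurious week 12 difference is the fraction lost × the week 3 gain: 0.10 × 0.2 = 0.02 SD up to 0.30 × 0.47 = 0.14 SD, in favour of ePain.

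**The case against.** Several stronger readings are tempting, and the protocol does not support them.

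- *Every early drop-out counts as exactly no change.* This fails for ePain participants lost between weeks 3 and 6, who carry a week 3 score on the primary outcome. The 0.33 SD in (a) holds only if nobody lost has any follow-up score.
- *Nearly a third of week 12 values will be copies.* The 30% is a recruitment allowance. The cited studies had 7.5% and 10%, where case (a) costs about 4 percentage points of power. Actual drop-out is not given.
- *The rule favours ePain.* The direction is not fixed. The ePain arm has the quizzes and the extra assessment, and controls gain access to ePain only by finishing follow-up, so heavier ePain loss is plausible. If both arms improve, that biases against ePain. The protocol gives no loss by arm and no shared improvement, so (c) is illustrative.
- *GEE makes replacement unnecessary, so the sentence can simply be struck out.* GEE does accept incomplete visits, but unweighted GEE on available data generally needs data missing completely at random. That would exchange one strong assumption for another.

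It is also fair that e-mail prompts and weekly reminders may reduce missed assessments, that incomplete items are flagged on submission, and that missing data will be examined in SPSS. None of these changes how a missing score is filled. Nor can the choice be treated as left to an unseen analysis plan, because the protocol makes it explicitly.

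**Conclusion.** The concern holds in this form: the protocol fixes a single replacement rule that partly assumes persistence at week 12, scores early losses on baseline or week 3 values that differ by arm, and presents copies as observations.

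Its size follows the realised drop-out. At 7.5–10% the dilution in (a) is 0.03–0.05 SD and the spurious persistence in (b) is about 0.05 SD at 10%. At 30% they reach about 0.14 SD each. Unequal loss matters only if it is marked and both arms change appreciably. All of these figures rest on the assumed loss timing and, for (a) and (b), on loss completely at random.

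The change should be made because the primary outcome is affected and better methods exist in the same software. The protocol does not show that the trial's result will be seriously wrong, or in which direction.

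**What to change.** Replace the carry-forward sentence with one of two primary approaches for weeks 6 and 12:

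1. a likelihood-based repeated-measures model fitted to all observed scores (SPSS MIXED); or
2. multiple imputation within arm from baseline and earlier scores, followed by the planned GEE.

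Do not substitute unweighted GEE on the available data. Keep all participants as randomised, and report drop-out by arm and visit. Add one sensitivity analysis that shifts the imputed self-efficacy scores of ePain drop-outs downward.

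No new data or software are needed. The cost is a little more analysis work and slightly wider confidence intervals, which reflect the missing data honestly. Because the rule is published and recruitment is complete, the change needs a dated amendment made before outcomes are examined by arm.

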## Discussion

Different studies using web-based programmes have demonstrated satisfactory results for their targeted populations [31, 32]. Using web-based programmes to administer health education to the public has become a trend due to the efficiency of this approach in getting in touch with and delivering information to participants [27]. As information technology develops more quickly, both hardware and software will greatly facilitate the spread of information to the public.

This study will adopt the self-efficacy theory of behavioural change to develop an intervention. ePain will provide step-by-step illustrations of pain knowledge and interventions for participants to improve their pain situations. People like to use self-initiated treatments to relieve pain [17]. ePain will provide information about different types of self-initiated treatments, including their correct use. Therefore, this study will use ePain to examine the improvement in the pain self-efficacy of the participants, which previous studies have yet to consider as a primary outcome [30].

The participants in ePain will benefit from improved pain self-efficacy and decreased pain intensity. They will be able to learn and understand pain as they go through the chapters. ePain will introduce various pharmacological and non-pharmacological interventions. The participants will be able to plan and choose their preferred pain relief methods. As psychological distress is associated with pain, the participants will experience lower levels of psychological distress. The anticipated effects of pain management can be sustained; ePain is an electronic pain management programme that will be available on the Internet for the public to access and it will be a cost-effective intervention.

One limitation of the study is the small size of the sample, which could limit the generalizability of the study. The calculation of the effect size is preliminary, based on a previous intervention study on pain intensity. Because there is no information about pain self-efficacy, our estimate of the size of the sample that will be required to determine a significant effect may be an underestimate or an overestimate. However, the optimal sample size can be calculated from the preliminary findings of the study after an accurate estimate is obtained of the standard deviation and the standardized effect size of the primary outcome variable ‘pain self-efficacy’. Another limitation of the study is the selection bias. Participants need to have access to the Internet or to have an electronic device to access the Internet to join the study.

This study will be the first in Hong Kong to examine the effectiveness of an electronic pain management programme that targets the working population. The programme will suit people’s work–life schedules and facilitate how they learn about and plan for pain management. Furthermore, ePain will contain Chinese cultural content that fits the needs of the Chinese population. Indeed, ePain will demonstrate a mix of the East and the West.

The study will attempt to improve the pain self-efficacy; pain intensity; levels of depression, anxiety, and stress; and quality of life of the working population. As an electronic pain management programme, ePain may offer an intervention that improves the pain and psychological status of the working population. Pain education materials can be delivered efficiently through the Internet. The contents of ePain will be tailor-made for the pain situations of the working population and be suitable for pain education. The results of the study will demonstrate how e-learning can help to improve the pain situations of the working population.

### Trial status

Protocol version 1 (23 October 2018). Recruitment began on 1 November 2018. Participant recruitment was completed on 1 January 2020.

This manuscript is re-submitted as recommended by the editor. The initial submission was in February 2019 (Manuscript ID: TRLS-D-19-00183) when the recruitment of participants was in progress.

The approximate date of completion is 1 April 2022.

## Data Availability

The datasets used and/or analysed during this study are available from the corresponding author on reasonable request.

## Abbreviations

BPI-C: Chinese version of the Brief Pain Inventory
CONSORT: Consolidated Standards of Reporting Trials
DASS-21: Depression Anxiety Stress Scale
ePain: Electronic pain management programme
PSEQ-HK: Chinese version of the Pain Self-Efficacy Questionnaire
SPIRIT: Standard Protocol Items: Recommendations for Interventional Trials
WHOQOL-BREF (HK): Hong Kong Chinese version of the World Health Organization Quality of Life Instruments
